### Measures

#### Primary Outcome: Evaluate New Tools to Improve Vaccination

The primary outcome of this study is the proportion of students in each group who initiate HPV vaccination by the end of the school year (at least one dose of the HPV vaccine).

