## Introduction

Human papillomavirus (HPV) is a widespread sexually transmitted infection that affects more than 1 in 5 people globally [1]. It is estimated that about 80% of men and women will be exposed to HPV at some point in their lives. With a global prevalence of 31% in men and 32.1% in women [2,3], HPV represents a major public health concern due to its established role in the development of multiple cancers [4], most notably cervical cancer, which remains the fourth most frequent cancer in women worldwide. The World Health Organization reported 660,000 new cervical cancer cases and 350,000 related deaths in 2022. In France, HPV is responsible for over 6400 cancers annually, including cervical, vulvar, vaginal, penile, anal, and oropharyngeal cancers. On Réunion Island, cervical cancer is the third most common cancer in women.

Prevention of cervical cancer is mainly based on screening with Papanicolaou (Pap) smear tests and HPV vaccination. Despite the proven safety and effectiveness of HPV vaccines in reducing the incidence of precancerous lesions and genital warts [5-7], vaccination coverage in France remains insufficient. As of 2023, only 45% of girls and 16% of boys aged 16 were vaccinated [8]. In Réunion Island, coverage is even lower: in 2022, only 12.7% of adolescents under 16 had received at least one dose of the HPV vaccine. Following the national vaccination campaign launched in 2023, only 6.8% of seventh-grade students were vaccinated at school in Réunion. Taking into account children vaccinated outside school by their general practitioner, the rate modestly increased to 27% for girls and 16% for boys. Nevertheless, these figures remain far from the thresholds needed to achieve herd immunity and effective cancer prevention [9].

The low uptake in Réunion Island may be attributed to a lack of information, fear of adverse events, and limited engagement from both health care professionals and families [10,11]. In countries such as Australia, Belgium, Portugal, and the United Kingdom, school-based HPV vaccination programs have achieved coverage rates exceeding 80% [12]. These programs reduce access barriers, promote equity, and provide opportunities for engaging educational interventions.

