### Study Objectives

The primary objective is to evaluate the impact of 2 awareness-raising strategies against HPV by involving middle school students to increase vaccination uptake. Specifically, we aim to compare the proportion of students who initiated vaccination before and after the interventions. In addition, we will assess motivations and challenges encountered in both the serious game and ambassador classes, as well as overall student satisfaction and knowledge.

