**Figure 2 figure2:**
[figure not shown]
Diagram showing the composition of colleges randomly assigned.

To calculate the required number of participants, the following assumptions are considered:

It is hypothesized that, by the end of the school year, 30% of students in the control group will have initiated vaccination. This estimate is based on vaccination coverage data published by Santé Publique France in 2023, which reported that 21.5% of children (girls and boys combined) aged 12 in Réunion had received at least one dose of the HPV vaccine by December 31, 2023 [23].It is hypothesized that the ambassador classes and the serious game will increase coverage to 45% in the respective intervention groups.A constant intracluster correlation coefficient of 0.1, considered a rather conservative value [24].An α risk of 5%90% powerThe average number of seventh-grade students (n) is 190 per college.A design effect (allowing intraclass correlation [ICC] to be taken into account) of 19.9, which is calculated as 1 + ICC × (n – 1).

Therefore, a total of 8 colleges per arm will be included, resulting in 24 colleges overall and approximately 3144 students.

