Follow-up visits.1. Visit 1 (T0)This visit will take place during school hours, just before the start of the awareness program (arms 2 and 3).Students will complete a questionnaire assessing their knowledge of human papillomavirus (HPV).The estimated completion time is a maximum of 10 minutes.2. Visit 2 (T1)This visit will take place during school hours, approximately 3 months after the end of the awareness program.Students will complete the same questionnaire to assess their postintervention knowledge.The estimated completion time is a maximum of 10 minutes.3. Visit 3 (T2)This visit will take place only in the middle schools assigned to the “ambassador classes” arm to assess the satisfaction of students receiving the intervention from their trained peers.A member of the research team will be present during the ambassador class intervention to ensure that essential information is accurately conveyed.The estimated completion time is a maximum of 10 minutes.4. Visit 4 (T3)At the end of the study, qualitative interviews will be conducted to explore the motivations and challenges experienced by teachers, parents, and students participating in the study.Each participant will receive information about the study and will provide consent for audio-recording of their interview.The interviews will then be transcribed anonymously using qualitative data analysis software.5. End of research visitThe end-of-research visit marks the final data collection, which may include qualitative interviews or vaccination data.This visit will also be used to collect information on HPV vaccination initiation during the school year (at least one dose counts) for each student, with assistance from the Social Security system via anonymized social security numbers.Within 1 year of the end of the research or its early termination, a final report will be prepared and signed by both the sponsor and the investigator.This report will be submitted to the competent authority.Additionally, the sponsor will provide the Committee for the Protection of Persons with a summary of the final report within 1 year of the study’s conclusion.

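### The primary endpoint is not fixed consistently: the planning rates are cumulative coverage, the final data collection is initiation during the school year, and the outcome definition has no start date

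*Protocol article*

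**What the plan says.** The Protocol article describes the endpoint in four places.

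- **Measures, Primary Outcome:** "the proportion of students in each group who initiate HPV vaccination by the end of the school year", with at least one dose required. The end of the window is fixed; the start is not.
- **Sample Size:** the control rate is that "by the end of the school year, 30% of students in the control group will have initiated vaccination". Its stated basis is that "21.5% of children (girls and boys combined) aged 12 in Réunion had received at least one dose of the HPV vaccine" by the end of 2023, which is ever-vaccinated coverage. The target is also called coverage: "the ambassador classes and the serious game will increase coverage to 45% in the respective intervention groups". The Expected Outcomes section repeats both rates in the same terms.
- **Textbox 2, End of research visit:** the visit is to "collect information on HPV vaccination initiation during the school year (at least one dose counts) for each student". This is incident initiation.
- **Study Objectives:** the aim is to "compare the proportion of students who initiated vaccination before and after the interventions", a third formulation.

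The Eligibility Criteria exclude only students whose parents oppose participation, so students with an earlier dose stay in.

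**The concern.** Year-end coverage and in-year initiation are different endpoints with different rates. A student who had a first dose before the school year is a success under the reading used for the sample size. Under Textbox 2 the same student is not an initiator, yet nothing removes that student from the denominator. Two statisticians working from this document could therefore code the same record in opposite ways.

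Two things follow. If in-year initiation is analysed, the sample size was planned on rates that belong to another endpoint. If year-end coverage is analysed, some students count as successes in every arm whatever the intervention does, and differences between schools in earlier uptake may add noise. The trial is open-label, so an endpoint left open until the data arrive also leaves room for a choice that should be made beforehand.

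**Working it through.** **1. How far apart the scales are.** The Results section reports 986/14,500 = 6.8% vaccinated in other Réunion schools during one campaign and 25/189 = 13.2% in the pilot school. These are school-campaign figures, so they do not estimate all in-year initiation, but they are far from 30% and 45%. If 21.5% were the share vaccinated beforehand, the planned in-year proportions over all students would be 30 − 21.5 = 8.5% and 45 − 21.5 = 23.5%.

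**2. Inputs for power.** From Sample Size: 30% vs 45%, ICC 0.1, m = 190 students per college, k = 8 colleges per arm, α 5%, power 90%. The test is 2-sided (Statistical Analysis). Assumed: b, the share with a dose before the school year, which the document does not give. Its nearby figures are 12.7% (Introduction, under 16, 2022), 14.8% (Expected Outcomes) and 21.5% (Sample Size); 5% is added as a low case.

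**3. The plan's own figure.** 217 per arm × design effect 19.9 = 4,318 students, and 4,318/190 = 22.7, so about 23 colleges per arm. The stated 8 is not reproduced. That is a separate problem, but it sets the reference power here.

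**4. Formula.** Effective n per arm = k·m/[1 + ICC(m − 1)]. SE = √{[p1(1 − p1) + p2(1 − p2)]/effective n}. Power = Φ(|p2 − p1|/SE − 1.96).

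**5. Year-end coverage.** Effective n = 1,520/19.9 = 76.4; SE = √(0.4575/76.4) = 0.0774; 0.15/0.0774 = 1.94; power 49%.

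**6. First dose in the year among students with none before.** Rates are (p − b)/(1 − b), with 190(1 − b) students per college and the 15-point gain over all students kept. For b = 21.5%: 8.5/78.5 = 10.8% and 23.5/78.5 = 29.9%; m = 149; design effect 15.8; effective n = 75.4; SE = 0.0637; power 85%.

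| Prior coverage b | Rates, control vs intervention | Power at ICC 0.1 |
|---|---|---|
| 5% | 26.3% vs 42.1% | 55% |
| 12.7% | 19.8% vs 37.0% | 67% |
| 14.8% | 17.8% vs 35.4% | 71% |
| 21.5% | 10.8% vs 29.9% | 85% |

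A pooled-variance version gives values one or two points lower. A t reference with 14 df gives 44% for year-end coverage and 80% for b = 21.5%.

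**7. Sensitivity to between-school variation, at b = 21.5%.** Holding ICC at 0.1 while the control rate falls from 30% to 10.8% lowers the implied control-arm between-school SD from √(0.1 × 0.30 × 0.70) = 0.145 to √(0.1 × 0.108 × 0.892) = 0.098.

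- ICC 0.15 on the new endpoint: power 70%.
- SDs held at their year-end values (0.145 and 0.157): SE = 0.0771; power 70%.
- All between-school variation in in-year uptake, so the SDs are divided by 0.785: SE = 0.0973; 0.191/0.0973 = 1.96; power 50%, no real gain over 49%.
- ICC 0.03 for both endpoints: year-end coverage already has about 92%, so there is little to gain.

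**8. The reverse case.** If 30% and 45% were in-year rates among unvaccinated students and b = 21.5%, year-end coverage would be 0.215 + 0.785 × 0.30 = 45.1% against 0.215 + 0.785 × 0.45 = 56.8%, with power 31%.

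**The case against.** The best defence is that the primary outcome wording can be read as initiation within the study year, in agreement with Textbox 2. That is fair. A reader might infer that the outcome definition itself says earlier doses count; it does not. The cumulative meaning comes from the planning rates, and the definition simply leaves the start open. The mismatch between planning rates and collected outcome remains under either reading.

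A reader might also infer that the 21.5% is the share vaccinated at study entry, and that restricting the analysis lifts power from 49% to 85%. The document does not support this. The figure is for children aged 12 who "had received at least one dose of the HPV vaccine by December 31, 2023", first doses are usually given in December, and the school campaign began in 2023. It may therefore already contain in-year doses. Removing the 6.8% vaccinated at school would leave 14.7%, as an illustration, and power of 70%. The 85% also needs an unchanged ICC of 0.1, which nothing in the document supports.

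Third, year-end coverage is unbiased under randomization, and coverage is the stated goal of the trial. That stands: the cumulative endpoint is a legitimate choice.

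Finally, baseline adjustment and the handling of students vaccinated earlier may be set out in the statistical analysis plan, which is not shown. The absence of a baseline covariate from the mixed model described under Study Limitations is therefore not counted as a defect. Which endpoint is primary, and which endpoint the planning rates describe, belongs in the protocol.

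**Conclusion.** The point holds as an inconsistency in the primary endpoint. The sample size rests on cumulative coverage, the final visit collects in-year initiation, the objective speaks of before and after, and the definition has no start date. This affects what is analysed and whether 30% and 45% apply to it.

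The effect on power is a possible loss of precision whose size is uncertain. It is not a bias. At ICC 0.1 with 8 colleges per arm, a restricted in-year endpoint has 67% to 85% power across the document's coverage figures, against 49% for year-end coverage. The gain falls to 6 points if prior coverage is 5%, and to almost nothing at 21.5% if school differences lie wholly in in-year uptake. Within the document's coverage figures no case at ICC 0.1 reaches the stated 90%, so settling the endpoint does not settle the number of colleges.

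**What to change.** Use one dated definition in Study Objectives, Sample Size, Primary Outcome and Textbox 2. Preferred: a first HPV dose dated between the start and the end of the school year, among enrolled students with no earlier dose, with year-end coverage in all students as a secondary outcome. Acceptable alternative: keep year-end coverage as primary, say that earlier doses count, and adjust for vaccination status at the start.

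Either way, request first-dose dates in the planned social security extract. Textbox 2 already implies that timing is needed, although the other sections mention only vaccination status, so availability must be confirmed. Restate the control and intervention rates for the chosen endpoint, and recompute power and the number of colleges over a range of prior coverage and ICC.

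The cost is wording, one more field in the extract and a new calculation. The preferred option also shrinks the primary denominator by the share already vaccinated, for example from 190 to about 149 students per college if that share is 21.5%. The study is expected to start in August 2026 and approvals are still in progress, so the change can be made before any data exist.

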#### Secondary Outcomes

The secondary outcomes are as follows:

Evaluate the proportion of girls and boys in each group who initiate HPV vaccination by the end of the school year.Explore and assess the motivations and challenges perceived by students in the ambassador classes and by those participating in the serious games.Evaluate overall student satisfaction within each arm for descriptive purposes.Compare students’ knowledge before and after the intervention in each arm.

#### Blinding

Given the nature of the interventions, blinding will not be implemented in this study. No participants will be blinded during the trial.

### Data Collection, Management, and Monitoring

Pre- and postintervention knowledge questionnaires will be identical for all students (Multimedia Appendix 1). Satisfaction questionnaires will be tailored to the specific trial arm—ambassador class or serious game—to evaluate the unique aspects of each intervention (Multimedia Appendices 2 and 3). Data collection via questionnaires will be anonymized and conducted at the class level.

Vaccination status will be collected with the assistance of the French social security system, following anonymization of social security numbers.

All information required by the protocol must be recorded in the observation notebooks, and any missing data must be explained. Data should be collected as they are obtained and transcribed neatly and legibly. Data will be entered into an electronic observation notebook (electronic case report form) using Ennov Clinical software.

A clinical research associate appointed by the sponsor will regularly visit the investigator center—at study initiation, periodically during the research depending on the inclusion rate, and at study completion. During these visits, and in accordance with the risk-based monitoring plan (considering participants, logistics, impact, and resources), the following elements will be reviewed:

Nonopposition from participantsCompliance with the research protocol and defined proceduresQuality of data collected in the observation notebook, including accuracy, completeness, and consistency with source documents (eg, medical records, appointment books, original laboratory results)

A written monitoring report will be prepared for each visit.

An audit may be conducted at any time by individuals mandated by the sponsor and independent of the research team. Its purpose is to verify participant safety and rights, ensure compliance with applicable regulations, and assess the reliability of the data.

An inspection may also be ordered by a competent authority (eg, ANSM [Agence nationale de sécurité du médicament et des produits de santé] in France).

Both audits and inspections may be conducted at any stage of the research, from protocol development to publication of results and the handling of data generated during the study.

Investigators agree to comply with the sponsor’s requirements for audits and with the competent authority’s requirements for inspections.

Four follow-up visits will be scheduled (Textbox 2).

Follow-up visits.1. Visit 1 (T0)This visit will take place during school hours, just before the start of the awareness program (arms 2 and 3).Students will complete a questionnaire assessing their knowledge of human papillomavirus (HPV).The estimated completion time is a maximum of 10 minutes.2. Visit 2 (T1)This visit will take place during school hours, approximately 3 months after the end of the awareness program.Students will complete the same questionnaire to assess their postintervention knowledge.The estimated completion time is a maximum of 10 minutes.3. Visit 3 (T2)This visit will take place only in the middle schools assigned to the “ambassador classes” arm to assess the satisfaction of students receiving the intervention from their trained peers.A member of the research team will be present during the ambassador class intervention to ensure that essential information is accurately conveyed.The estimated completion time is a maximum of 10 minutes.4. Visit 4 (T3)At the end of the study, qualitative interviews will be conducted to explore the motivations and challenges experienced by teachers, parents, and students participating in the study.Each participant will receive information about the study and will provide consent for audio-recording of their interview.The interviews will then be transcribed anonymously using qualitative data analysis software.5. End of research visitThe end-of-research visit marks the final data collection, which may include qualitative interviews or vaccination data.This visit will also be used to collect information on HPV vaccination initiation during the school year (at least one dose counts) for each student, with assistance from the Social Security system via anonymized social security numbers.Within 1 year of the end of the research or its early termination, a final report will be prepared and signed by both the sponsor and the investigator.This report will be submitted to the competent authority.Additionally, the sponsor will provide the Committee for the Protection of Persons with a summary of the final report within 1 year of the study’s conclusion.

### Statistical Analysis

Analyses will be performed by the biostatistics team at La Réunion University Hospital, in collaboration with the study methodologist and coordinating investigator, according to the statistical analysis plan established before database lock. Analyses will be conducted using SAS (version 9.4; SAS Institute Inc), Stata (version 16; StataCorp), or R (R Foundation) software.

Qualitative variables will be described using counts and percentages. Quantitative variables will be summarized using the mean and SD, or the median and range, as appropriate.

Comparative analyses of the end points will be conducted according to the intention-to-treat principle, meaning that students will be analyzed in the group to which their class was randomized, regardless of any deviations from the research protocol. All students included and followed until the end of the school year will be considered in the analysis.

At the college level, the main deviation from the expected research protocol is nonparticipation in the intervention allocated by randomization.

At the student level, expected deviations from the protocol include occasional absenteeism during data collection at different periods, permanent departure from college during the academic year, or individual refusal to participate at any point during the study. These factors may lead to a loss of statistical power and could affect the generalizability of the findings. Statistical significance will be set at *P*<.05 (2-sided).

The results of this study will be published in accordance with the CONSORT (Consolidated Standards of Reporting Trials) recommendations extended to cluster randomized trials.

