## Methods

### Trial Design

This is a randomized, controlled, open-label intervention study based on 2 awareness strategies for HPV vaccination in Réunion Island. A prototype of the serious game was created in May 2025, and the service company will devote several weeks to producing the final materials. The card game is expected to be ready for the start of the school year.

Colleges (selected from lists provided by the local education authority in March-April) will then be randomly assigned to 3 groups, with 8 colleges per arm:

Reference arm: no intervention; schools will only follow the government’s vaccination campaign.Ambassador arm: implementation of specific HPV vaccine education to create an ambassador class.Serious game arm: distribution of the card-based serious game.

The unit of randomization will be the middle school. Each school will be assigned to 1 of the 3 intervention arms (1, 2, or 3) according to a randomization list. The allocation ratio will be 1:1:1, with stratification by middle school level. To minimize imbalance between schools, a constrained randomization plan will be used (PROC PLAN; SAS Institute Inc). The randomization list will be generated by a statistician at the Methodology and Data Management Center before the start of the study. A document describing the randomization procedure will be kept confidential within the same center.

The directors of the randomized schools will be invited to participate in the study. Our study is supported by the rectorship of Réunion Island, which has already written to all directors to request their assistance with this project.

Once school directors agree, they will be asked to identify 1 or 2 teachers, on a voluntary basis, to help implement the study in each school. From our experience, teachers are highly motivated to take part in public health initiatives, particularly those involving playful learning.

If directors decline participation, a new randomization will be conducted in additional schools to ensure school buy-in.

Interventions will be conducted only in seventh-grade classes, targeting children around 12 years of age.

All participants will complete an HPV baseline knowledge questionnaire before the intervention and again up to 3 months afterward.

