#### Intervention Group: Ambassador Class (Peer Learning)

For each college randomized to this arm, 1 seventh-grade class will be randomly selected as the ambassador class. If a college has more than 5 seventh-grade classes, 2 ambassador classes will be designated (Figure 2). Students in the ambassador class will receive the intervention during a single class period.

This group will receive a 30-minute presentation on HPV delivered by a trained facilitator during class. The presentation will be standardized and consistent across all participating classes to minimize potential bias. Developed in advance by a team of experts, it will remain identical for all classes in this intervention arm. The presentation will cover key topics, including HPV, its epidemiology in France and Réunion Island, its benign and malignant sequelae, and preventive measures such as screening and vaccination. To assess students’ understanding of the material, they will complete a satisfaction questionnaire following the presentation.

The same preintervention (T0) and postintervention (T1) questionnaires used in the control group to assess HPV knowledge will be administered.

This arm, which integrates peer learning, will train “ambassador classes” on HPV prevention. In a second step, these students will disseminate the information to their peers in other seventh-grade classes within their middle school (T2). They will have the autonomy to choose the format for delivering the information during class (eg, games, presentations, films, posters, slideshows, comics [20]). Students who receive the information from their peers will also complete a satisfaction questionnaire. A field coordinator (a volunteer teacher) will be present during the training sessions to ensure that essential information is effectively conveyed and, if necessary, to supplement any important details that may have been omitted in the student-led presentations.

Vaccination status will be collected using the French social security system after anonymization of social security numbers (T3).

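### The intention-to-treat rule and the followed-to-year-end population conflict for students who leave their school, and on its plain reading the second rule is an unnecessary completer set

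*Protocol article*

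**What the plan says.** All of the following is in the protocol article.

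- **Principle** (Statistical Analysis): the comparison is by intention-to-treat, so that "students will be analyzed in the group to which their class was randomized, regardless of any deviations from the research protocol".
- **Population** (same section, next sentence): "All students included and followed until the end of the school year will be considered in the analysis".
- **Expected deviations** (same section): among the student-level deviations is "permanent departure from college during the academic year", beside occasional absence and individual refusal. Their stated consequence is: "These factors may lead to a loss of statistical power and could affect the generalizability of the findings". Bias is not mentioned.
- **Outcome source** (follow-up visits textbox under Data Collection, Management, and Monitoring): initiation of vaccination is collected "for each student, with assistance from the Social Security system via anonymized social security numbers". Settings, the three arm descriptions under Intervention, and Study Limitations name the same source.
- **Unit of allocation** (Trial Design): "The unit of randomization will be the middle school". The only random step at class level is inside the ambassador arm, where "1 seventh-grade class will be randomly selected as the ambassador class".

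**The concern.** The two rules give different answers for a student who changes school during the year. Two statisticians following the same section could use different denominators for the primary outcome.

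If the second rule prevails, students are selected on something that happens after randomization. The trial is unblinded, the interventions promote vaccination, and parents may withdraw a child at any time. Departure or withdrawal could therefore be related to both arm and attitude to the vaccine. If so, the randomized comparison is no longer protected. Study Limitations presents the objective, record-based endpoint as compensation for the lack of blinding, and a completer rule gives part of that protection away.

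**Working it through.** **1. The rules applied to one leaver.** Take a student included in September who moves to another school before July.

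- Departure is on the section's own list of deviations, and the principle applies regardless of deviations. The student stays in.
- The population sentence requires follow-up to the end of the school year. Departure is one of the losses the section itself names, so the plain reading takes the student out.
- The outcome is at least one dose by the end of the school year, read from social security records. Nothing in that route depends on which school the student attends in July. The outcome of a leaver whose data may be used is not missing merely because the student left.

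**2. Possible bias.** One input comes from the plan: Sample Size assumes that "30% of students in the control group will have initiated vaccination". No leaver rate is stated, so the leaver share L and the leavers' coverage v are assumptions. True coverage is set to p = 30% in both arms, so any difference is spurious.

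Coverage among completers = (p − L × v) / (1 − L)

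Shift within one arm:

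- L = 5%, v = 15%: (0.300 − 0.0075) / 0.95 = 30.8%
- L = 10%, v = 15%: (0.300 − 0.015) / 0.90 = 31.7%
- L = 5%, v = 0%: 0.300 / 0.95 = 31.6%
- L = 10%, v = 0%: 0.300 / 0.90 = 33.3%

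These shifts are not the bias. The bias is the difference between arms:

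| Control L, v | Intervention L, v | Control completers | Intervention completers | Spurious difference |
|---|---|---|---|---|
| 5%, 30% | 5%, 15% | 30.0% | 30.8% | 0.8 points |
| 5%, 15% | 10%, 15% | 30.8% | 31.7% | 0.9 points |
| 5%, 30% | 10%, 15% | 30.0% | 31.7% | 1.7 points |
| 10%, 30% | 10%, 15% | 30.0% | 31.7% | 1.7 points |
| 5%, 15% | 10%, 0% | 30.8% | 33.3% | 2.5 points |

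If L and v are the same in both arms, the difference is zero. If all included students are kept, it is zero in every row.

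**3. Power.** The plan's design effect reproduces: 1 + 0.1 × (190 − 1) = 19.9. With 8 colleges per arm and m students analysed per college:

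Effective n per arm = 8m / (1 + 0.1 × (m − 1))

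Power = Φ[(0.15 × √n − 1.96 × √(2 × 0.375 × 0.625)) / √(0.30 × 0.70 + 0.45 × 0.55)], where n is the effective n.

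| Leavers dropped | m | Effective n per arm | Power |
|---|---|---|---|
| 0% | 190 | 1520 / 19.9 = 76.4 | 48.2% |
| 5% | 180.5 | 1444 / 18.95 = 76.2 | 48.1% |
| 10% | 171 | 1368 / 18.0 = 76.0 | 48.0% |
| 15% | 161.5 | 1292 / 17.05 = 75.8 | 47.9% |

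The starting level is far from the planned 90%. That is a separate sample-size matter, and only the change counts here. At the stated intracluster correlation, information depends on the number of schools, so losing 15% of students costs about 0.3 points of power. The section expects these deviations to cost power, but for dropped leavers that cost is close to nil. Possible bias is the real issue.

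**4. Class or school.** Each class sits in one school and so in one arm. Reading class or school in the allocation sentence puts every student in the same arm.

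**The case against.** The strongest reply is that the plan never says leavers are dropped. The population sentence does not contain the word only, and it leaves follow-up undefined. If being followed means being traceable in the social security records, a student who changes school is still followed, and the two sentences agree for the primary outcome. A reader might infer that the plan openly excludes leavers. The text does not go that far; it contradicts itself. What remains is that departure from the school is a loss the section names, and it expects such losses to cost power. Exclusion is therefore the plain reading, and the wording needs settling.

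A reader might also take the class wording for an allocation error. It is not one. Trial Design fixes the school as the unit, Recruitment and Study Limitations agree, and no student's arm changes.

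A third inference would be that a bias of a given size has been shown. It has not. The documents give no leaver rate and no evidence that departures differ between arms. Equal leaving with equal coverage produces no bias when there is no true effect.

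Nor can every outcome be recovered. Parents may object or withdraw a child, and those records may be legitimately unusable. The documents also do not say when identifiers are captured, so it is not established that the planned records request already covers leavers.

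Finally, details of analysis sets usually belong in the statistical analysis plan. That would answer a point about missing detail. It does not answer two adjacent sentences in the protocol that conflict.

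**Conclusion.** The point stands as a contradiction in the stated analysis population, with a completer set as the plain reading of the second sentence. The exclusion serves no purpose for the primary outcome. It opens the way to selection after randomization in an open-label trial.

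The size of any bias is unknown. Under assumed leaver shares of 5-10%, leaver coverage between 0% and 30%, and a pattern that differs between arms, it is about 1 to 2.5 points in either direction, depending on which arm loses its unvaccinated students. That is modest beside the planned difference of 45% − 30% = 15 points. The cost in power is negligible. This should be corrected before the trial starts, but it does not threaten the design. The class wording is a slip only.

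**What to change.** Replace the two sentences with a rule on these lines:

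- All students included at the September enrolment are analysed in the arm to which their school was randomized, including those who later change school, miss sessions or miss questionnaires.
- Vaccination status is taken from social security records for all of them, except where use of the data has been refused or withdrawn.
- An analysis restricted to students still followed at the end of the school year may be reported as a sensitivity analysis.

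Anchor the population on September enrolment (Settings) and not on attendance at the T0 questionnaire. T0 takes place just before the awareness programme, so its date can vary by school and arm. Tying inclusion to it could again lose students after randomization.

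The new wording also replaces class with school, in line with Trial Design.

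The cost is two sentences, plus a check that the identifiers needed for the records request are obtained at enrolment. The Results section puts the start at August 2026, so the change can be made before any student is enrolled.
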